## Methods

### Design

A prospective cohort study will be conducted in an Australian hospital-based phase II CR program over 12-months. Baseline data from this study will contribute to an international, multi-centre cross-sectional study (Australia, New Zealand, United States of America, South Africa, Spain, and Portugal). At baseline, participants will be assessed within the first 2 weeks after enrolment in the phase II CR program. In Australia, participants will be assessed again within 2 weeks of finishing the 6-week phase II CR program, and at 6 and 12-months following admission into the phase II CR program. The phase II cardiac CR program included in this study is typical of most contemporary CR programs in Australia. The CR program is multidisciplinary, time-limited (twice a week, 6-weeks), conducted in groups, hospital-based, and has educational and supervised exercise components (one hour education plus one hour exercise) [4].

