### Recruitment

CR nursing staff will recruit consecutive participants for this study within CR sessions. CR Staff will identify potential participants on admission to the phase II CR program and will provide them with details of the study. If potential participants are interested in taking part in the study, CR nursing staff will determine whether they are eligible according to the study inclusion and exclusion criteria, and gain participants’ consent. The flow of participants through the trial is illustrated in Fig. 1. The principal investigator (PI) will visit the CR team prior to participant recruitment and explain the study protocol to all team members. The PI will remain in contact with eligible participants and organise 6 and 12-month data collection to maintain participant retention. If participants are lost to follow-up, any data that has been collected will be used in the data analysis.

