### Outcome measures

All study measures will be collected at baseline, 6-weeks, 6 and 12 months. All assessments will be conducted at the hospital where the CR program takes place, and will be carried out by a trained health professional. This excludes the blood samples, which will be collected at pathology collection centres. The PI will ensure that all assessors comply with data collection protocols to promote data quality and minimise measurement error.

The main outcome measures are sedentary behaviour and physical activity levels objectively measured using an accelerometer. Subjective measures of sedentary behaviour (Past-Day Adults’ Sedentary Time questionnaire, PAST) and physical activity (Active Australia Survey, AAS) have also been included in this study as they are commonly employed as outcome measures in the clinical setting due to their low cost and ease of use [19]. Haskell also suggests that physical activity data is best interpreted by adopting a combination of objective and subjective measures [20]. Dependent variables include body mass index (BMI), waist-to-hip ratio (WHR), blood lipid and glucose levels, exercise capacity (6-min walk test, 6MWT), quality of life (MacNew Heart Disease Health-related Quality of Life Questionnaire, MacNew) and anxiety and depression (Hospital Anxiety and Depression Scale, HADS).

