### Sample size

The G*Power software v.3.1.9.2 was used to *a priori* determine the required sample size. Previous recommendations for sample size estimation in Multiple Linear Regression problems were used [32]. With a desired effect size of f^2^ = 0.5 (large), given a maximum of 10 predictor variables including potential confounders, a sample size of *n* = 59 is needed to achieve a power of 0.95 in a test based on α = 0.05. Assuming a dropout rate of 25 %, 75 participants will be recruited for the Australian study.

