### Statistical analysis

The number of minutes per day spent in sedentary behaviour will be calculated using standard count-based intensity threshold values of counts per minute: < 100 for sedentary behaviour (<1.5 MET). Four further summary measures of sedentary behaviours will calculated per day and averaged over valid days: (a) percentage of the wear-day spent in sedentary behaviour (b) number of sedentary bouts (defined as a period of consecutive minutes where the accelerometer registered <100 counts/minutes) (c) average duration of sedentary bouts and (d) number of sedentary breaks (defined as at least 1 min where the accelerometer registered ≥ 100 counts/minute following a sedentary bout). The Freedson Combination energy expenditure algorithm will be used to determine the intensity cut-points for MVPA. This outcome variable will be used to investigate whether participants have reached the World Health Organisation physical activity guidelines.

Linear regression models will be performed at each data collection point, where the dependent variables will be each of the health variables available. The models will have the different summary measures of sedentary behaviour (i.e. one model will be performed with each one) as main independent variables, and models will also be performed for MVPA and each of the different physical activity intensities (i.e. light, moderate and vigorous physical activity). If it is the case, quadratic trends might be explored. The models will be adjusted for total time of activity (i.e. counts per min ≥ 100), gender, socioeconomics variables, BMI and other potential confounders available.

Additional analyses will be completed with a one-way repeated measures analysis of variance (ANOVA) to test for differences in physical activity and sedentary behaviour (with a 95 % confidence interval (CI)) within the Australian sample over 12 months. Intention-to-treat analysis will be used at 6-weeks, 6 and 12-months where data is missing, bringing the last value forward. A maximum of three attempts will be made to contact participants so outcome measures can be obtained, making the analysis more complete.

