## Discussion

Over 12 months we will assess the physical activity, sedentary behaviour levels and health outcomes of those with CHD attending a hospital-based phase II CR program. Specifically, we will measure the physical activity and sedentary behaviour levels of participants’ with CHD at the start of a phase II CR program, at the end of the program, and at 6 and 12-months to determine the short and medium-term changes in physical activity and sedentary behaviour levels. Few studies have determined whether those attending CR achieve the public health physical activity guidelines, as recommended, over the short and medium term, and no known studies have reported on CR participants’ sedentary behaviour, or sitting time. Importantly, we will also investigate the relationships between physical activity, sedentary behaviour and health outcomes at each point-in-time to determine the potential, independent risk of these behaviours, including the potential for the ACP phenomenon in CR participants.

One of the strengths of the trial is the pooling of baseline results from multiple sites, internationally. Combining data will increase the strength of statistical power analyses, with the sample size to be recruited providing adequate statistical power to detect relationships between the variables. The Australian single cohort study is prospective, allowing all the relevant information to be collected, including the objective and subjective measurement of physical activity and sedentary behaviour. The outcome measures are also collected in a ‘real-world’ situation, reflecting common practice for CR in Australia.

Limitations to the study include multiple assessors of outcome measures despite assessors remaining consistent for each outcome measure, for example, exercise capacity will always be assessed by an exercise physiologist. There is also a lack of randomisation, with recruitment of participants occurring consecutively. Other possible limitations include the potential for loss of participants to follow-up, and few participants achieving the outcome of interest, the ACP phenomenon.

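### Carrying the last value forward, labelled intention-to-treat, biases the 12-month change in a single cohort, in a direction and by an amount that cannot be known in advance

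*Protocol article*

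**What the plan says.** All statements are in the protocol article.

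- **Missing-data rule (Statistical analysis).** "Intention-to-treat analysis will be used at 6-weeks, 6 and 12-months where data is missing, bringing the last value forward". No other method for missing values, and no sensitivity analysis, is named.
- **Analysis of change (same paragraph, immediately before).** "Additional analyses will be completed with a one-way repeated measures analysis of variance (ANOVA) to test for differences in physical activity and sedentary behaviour" in the Australian sample over 12 months, with a 95% confidence interval.
- **Design.** "A prospective cohort study will be conducted in an Australian hospital-based phase II CR program over 12-months". The Discussion adds: "There is also a lack of randomisation, with recruitment of participants occurring consecutively".
- **Visits (Outcome measures).** "All study measures will be collected at baseline, 6-weeks, 6 and 12 months".
- **Expected loss (Sample size).** "Assuming a dropout rate of 25 %, 75 participants will be recruited for the Australian study". The timing of dropout is not given.
- **Recruitment.** For people lost to follow-up, "any data that has been collected will be used in the data analysis". This commits to using what was observed. It does not itself prescribe carrying values forward.

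**The concern.** There are two separate problems.

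The first is the label. Intention-to-treat means analysing people by the treatment they were assigned. Nothing is assigned in this cohort. The term here describes single imputation only, and gives it an authority that it does not have.

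The second is the method. The Discussion says the study will determine short- and medium-term change in activity and sedentary behaviour. Carrying a value forward supplies the answer for everyone who leaves: no further change. With 25% lost, 0.25 × 75 = 18.75, so about 19 of the 75 values analysed at 12 months could be copies of earlier ones. A claim that behaviour is maintained after rehabilitation could then be produced partly by the imputation, and a true late change could be diluted. The copies also enter the analysis as if measured, so the interval is narrower than the observed 12-month data give.

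**Working it through.** **The plan's own figure.** The only calculated figure is n = 59 for the regression (f² = 0.5, 10 predictors, α = 0.05, power 0.95). It reproduces: the noncentral F test with λ = 0.5 × N gives power 0.952 at N = 59 and 0.947 at N = 58. It says nothing about the analysis of change, for which the article gives no figure.

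**Inputs.** From the article: N = 75, 25% dropout, visits at baseline, 6 weeks, 6 and 12 months. Assumed, because the article gives none: dropout completely at random (a favourable case), SD 1 at each visit, within-person correlation r = 0.6, and the trajectories and dropout timings below.

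**Bias.** Let d be the true change from baseline to 12 months, and m_k the mean change already reached at last visit k, where a share p_k of the cohort stops. Then

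bias = Σ p_k × (m_k − d).

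- All dropout after baseline: 0.25 × (0 − d) = −0.25d, so 75% of the change is recovered.
- Gain reached at 6 weeks and kept, dropout spread evenly over the three possible last visits: (0.25/3) × (−d) = −0.083d, so about 92% is recovered.
- Change linear in time (12.5% reached at 6 weeks, 50% at 6 months), dropout spread evenly: (0.25/3) × (1 + 0.875 + 0.5) = 0.198, so about 80% is recovered.
- Gain kept, all dropout after 6 weeks: 0.25 × (d − d) = 0.
- Gain of 0.5 SD at 6 weeks, fully lost by 12 months (d = 0), all dropout after 6 weeks: 0.25 × (0.5 − 0) = +0.125 SD, away from zero.
- Gain of 0.5 SD at 6 weeks, falling to 0.2 SD at 12 months, all dropout after 6 weeks: 0.25 × (0.5 − 0.2) = +0.075 SD, also away from zero.

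**Standard errors.** The variance of an observed change is 2(1 − 0.6) = 0.8. With 75 × 0.75 = 56.25 observed pairs, the observed-data SE is √(0.8/56.25) = 0.119. With all dropout after baseline, the carried-forward variance is 0.75 × 0.8 + 0.75 × 0.25 × d².

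**Coverage, worked once.** Take d = 5 × 0.119 = 0.596 with all dropout after baseline. The variance is 0.6 + 0.1875 × 0.596² = 0.667, so SE = √(0.667/75) = 0.094. The bias is −0.149, which is 1.58 SEs. Coverage is about Φ(1.96 − 1.58) = 0.65.

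In the relapse case the variance is 0.8 + 0.1875 × 0.5² = 0.847, so SE = 0.106. The bias of 0.125 is 1.18 SEs, and coverage is about 0.78. With a t rather than a normal critical value it is 0.79.

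**Coverage of the 95% interval, by pattern.** Simulation and closed form agree to about 0.01.

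| Trajectory and dropout | d = 2 SE | d = 3 SE | d = 5 SE |
|---|---|---|---|
| All dropout after baseline | 0.90 | 0.83 | 0.65 |
| Linear change, dropout spread evenly | 0.92 | 0.89 | 0.79 |
| Gain kept, dropout spread evenly | 0.95 | 0.94 | 0.92 |
| Gain kept, all dropout after 6 weeks | 0.95 | 0.95 | 0.95 |

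For the full relapse (d = 0), coverage is about 0.79 at r = 0.6, and between 0.73 and 0.82 for r between 0.7 and 0.5. The interval then excludes zero in 19–27% of studies although nothing has changed. Observed 12-month data alone gave 0.945–0.958 in every scenario run.

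**Interval width.** Over the scenarios run at r = 0.5 and 0.7, the carried-forward interval was 0.74–0.91 of the width of the observed-data interval. With no true change at any visit, its coverage was still 0.95.

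**The case against.** Four stronger readings are tempting, and the documents do not support them.

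- **That the rule always biases toward no change, by 25%.** A reader might infer this from the 25% dropout. It holds only if every lost participant's last visit is baseline, or if nothing had changed before they left. The article gives no dropout timing, and the relapse case goes the other way.
- **That the narrow interval is a second, independent error.** With no true change, coverage stayed at 0.95. For the mean change, the undercoverage comes from bias around a narrower interval, and should not be counted twice.
- **That copied exposure–outcome pairs will be reported as 6- and 12-month associations.** The rule follows the repeated-measures ANOVA. The per-visit regressions stand in the paragraph before, without mention of imputation, and their sample size is inflated for dropout, which would be unnecessary if carried values kept everyone in. On the other hand, the rule names the follow-up visits without limiting itself to the ANOVA. The text is ambiguous.
- **That the primary analysis is affected.** The article calls the ANOVA additional, and sizes the study on the regression. Baseline regressions and the international baseline analysis are untouched.

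The article also limits the damage: the investigator stays in contact with participants, up to three contact attempts are made, and loss to follow-up is listed as a limitation. These measures reduce the amount of missing data. They do not make the stated rule valid for what remains. Nor is this a detail left to an analysis plan, because the article states the rule.

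**Conclusion.** The point stands in this form. The label is wrong for a single non-randomised cohort. The only stated missing-data rule biases the 12-month change, even under completely random dropout, whenever mean behaviour changes after the last visit attended and the carried gaps do not happen to cancel. The direction and size depend on unknown trajectories and dropout timing. Under the assumptions above, the bias runs from −0.25 of the true change, through zero, to a false +0.125 SD. Coverage at a true change of 5 observed-data SEs runs from about 0.65 to 0.95, and is about 0.79 under full relapse. Dropout related to behaviour was not modelled and could change these figures. What is at risk is the description of change over 12 months, which is a stated aim. The baseline results are not affected.

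**What to change.** 1. Delete the term intention-to-treat.
2. Replace the repeated-measures ANOVA with carried values by a likelihood-based linear mixed model, with visit as a factor, fitted to all observed visits. It is valid under missing at random and fits the Recruitment section's commitment to use the data collected.
3. State that the 6- and 12-month regressions use values observed at that visit, not carried values.
4. Keep last value forward at most as a sensitivity analysis.

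The cost is analysis wording and somewhat wider intervals. No change to recruitment, visits or measurements is needed.

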### Ethical approval

This study was approved by the ACT Health Human Research Ethics Committee in August 2015 (Project reference: ETH.5.15.076).

### Trial status

Study protocol.

## Discussion

Over 12 months we will assess the physical activity, sedentary behaviour levels and health outcomes of those with CHD attending a hospital-based phase II CR program. Specifically, we will measure the physical activity and sedentary behaviour levels of participants’ with CHD at the start of a phase II CR program, at the end of the program, and at 6 and 12-months to determine the short and medium-term changes in physical activity and sedentary behaviour levels. Few studies have determined whether those attending CR achieve the public health physical activity guidelines, as recommended, over the short and medium term, and no known studies have reported on CR participants’ sedentary behaviour, or sitting time. Importantly, we will also investigate the relationships between physical activity, sedentary behaviour and health outcomes at each point-in-time to determine the potential, independent risk of these behaviours, including the potential for the ACP phenomenon in CR participants.

One of the strengths of the trial is the pooling of baseline results from multiple sites, internationally. Combining data will increase the strength of statistical power analyses, with the sample size to be recruited providing adequate statistical power to detect relationships between the variables. The Australian single cohort study is prospective, allowing all the relevant information to be collected, including the objective and subjective measurement of physical activity and sedentary behaviour. The outcome measures are also collected in a ‘real-world’ situation, reflecting common practice for CR in Australia.

Limitations to the study include multiple assessors of outcome measures despite assessors remaining consistent for each outcome measure, for example, exercise capacity will always be assessed by an exercise physiologist. There is also a lack of randomisation, with recruitment of participants occurring consecutively. Other possible limitations include the potential for loss of participants to follow-up, and few participants achieving the outcome of interest, the ACP phenomenon.

One third of all heart attacks in Australia are repeat events, they are more likely to result in death and are costly. If sedentary behaviour is found to be an important consideration for secondary prevention of CHD, reducing sedentary behaviour, or sitting time, may be a feasible additional or first-line strategy to improve the health of those with CHD, alongside traditional recommendations to increase the time spent in moderate-to-vigorous intensity physical activity. Therefore, the outcomes from this study may have implications for CR research, policy and practice, and ultimately improve the health of those with CHD.
